# Cut off points

The study will be suspended if recruitment of dentists will not reach the estimated

numbers per cities during 6-9 month.

The study will be suspended, if failure rate reaches more then 5% of the fillings in the

first year.

The study will be suspended, if response will be below 60% of the examination each

year in respect to the year before.

Not used materials will be sent back to GC.

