# Duration

5 years after the recruiting of participating dentists in their own dental practice

(proposed period of recruiting: 0.5 y, proposed period of treatment of participants:

0,5 y). Yearly Follow-up: start point: first placed filling).

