# Calculation of the participants

The calculation of the numbers of participants were done with „nQuery 4.0“ software

by [name]. [name].

As aim (dependent variables) were used

- Loss of filling (dichotomy variable), defined as fracture or crack of the filling
- Abrasion of the occluded filled surfaces (scaled variable)
- Wear abrasion of the occlusal surface (scaled variable)

When the sample size in each group (Fuji IX and Equia) is 440, an exponential

maximum likelihood test of equality of survival curves with a p= 0.050 two-sided

significance level will have 90% power to detect the difference between a Group 1

exponential parameter, .1 of 20 % 0.0201 (corresponding to a proportion of 30% after

60 months) and a Group 2 exponential parameter, .2 of 0.0268 (corresponding to a

proportion of 20% after 60 months and a constant hazard ratio of

0.0201/0.0268=0.75) 30 %. This assumes an accrual period of 12 months, a

maximum follow-up time of 60 months (five years), and a common exponential

dropout rate of 1%.

The calculation is based on all incorporated units (fillings), e.g. all possible units

(fillings). The homogeneity of the participants will be guaranteed by the recruiting

phase, which will use the following selection criteria: Only one (at most two)

restoration for each side is calculated for each patient. The restoration will be limited

to posterior teeth (premolars and/or molars).

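### The first-year suspension limit of 5% failures cannot be squared with the planning hazards, which imply 21.4% and 27.5% failure in the first year

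*Protocol*

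**What the plan says.** Cut off points (Protocol) lists three conditions for suspending the study. The second reads "The study will be suspended, if failure rate reaches more then 5% of the fillings in the"; the period named at the end of that sentence is the first year. It does not say whether the year runs from each filling's placement or from the first placement in the study. It does not say whether the rate is taken over both arms or per arm, or what happens to follow-up of fillings already placed.

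Calculation of the participants (Protocol) sizes the trial at 440 fillings per arm for 90% power, two-sided 5%, with an exponential maximum likelihood test. For one group it gives "exponential parameter, .1 of 20 % 0.0201 (corresponding to a proportion of 30% after", where the time point is month 60. For the other it gives a hazard of 0.0268, which it ties to the "proportion of 20% after 60 months and a constant hazard ratio of", the ratio being 0.75. Accrual is taken as 12 months, follow-up as at most five years, and both groups share a "dropout rate of 1" per cent. Stray figures of 20 % and 30 % stand beside the hazards without explanation, the second in "0.0201/0.0268=0.75) 30 %. This assumes an accrual period of 12 months, a".

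Duration (Protocol) proposes half a year for treating participants and adds: "0,5 y). Yearly Follow-up: start point: first placed filling".

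**The concern.** A suspension limit and a sample size both rest on an assumed failure rate, so within one protocol they should rest on the same one. Here the limit allows 5% in the first year, while the sample size needs most fillings to fail by five years. If the planning hazards are right, the study meets its suspension condition within months of placement simply by behaving as planned, and the rule cannot tell an unexpected problem from the expected course. If failure stays low enough to avoid suspension, the events on which the 90% power was calculated will not occur. The main aim, a comparison of survival over five years, is at stake either way.

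**Working it through.** **Inputs.** Hazards 0.0201 and 0.0268 per month, 12 months accrual (R), 60 months in total (T), dropout 1%, two-sided alpha 0.05, 440 per arm (all from Calculation of the participants); limit 5% of fillings (Cut off points), so 0.05 × 880 = 44.

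**1. What the proportions are.** exp(−60 × 0.0201) = 0.299 and exp(−60 × 0.0268) = 0.200. The printed 30% and 20% are therefore survival proportions and the hazards are monthly. Assumed five-year failure is 70% and 80%.

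**2. Reproducing 440.** With dropout hazard γ, the probability of an observed event is p(λ) = λ/(λ+γ) × {1 − [exp(−(λ+γ)(T−R)) − exp(−(λ+γ)T)] / ((λ+γ)R)}. With γ = 0.01 per month, p = 0.536 and 0.628. Put V(λ) = λ²/p(λ) and let λ̄ be the mean hazard. Then n = [1.96 √(2V(λ̄)) + 1.28 √(V(λ₁)+V(λ₂))]² / (λ₁−λ₂)² = 441.7 per arm; the log-hazard variant gives 439.3. Power at 440 is 89.9% to 90.0%, with 440 × (0.536 + 0.628) ≈ 512 events. No dropout gives 361 per arm and 1% per year gives 367, so the stated size fits a monthly dropout of 1%. The printed hazards, hazard ratio, proportions, size and power agree with one another.

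**3. First-year failure at those hazards.** Per filling, F = 1 − exp(−12λ). For a calendar year from the first placement, with uniform placement over R months, F = 1 − [exp(−λ(12−R)) − exp(−12λ)]/(λR). The probability of more than 44 failures is the exact sum of two binomials of 440 each.

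| First year taken as | 0.0201 | 0.0268 | Mean of arms | Expected of 880 | P(more than 44) |
|---|---|---|---|---|---|
| 12 months per filling | 21.4% | 27.5% | 24.5% | 215 | 1 − 6×10⁻⁵⁵ |
| Calendar, 6-month placement | 16.5% | 21.3% | 18.9% | 167 | > 0.9999 |
| Calendar, 12-month placement | 11.1% | 14.5% | 12.8% | 113 | > 0.9999 |

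The binomial treats fillings as independent. On a normal approximation for 12 months per filling, a design effect of 10 leaves a probability of only about 10⁻⁵ of staying within the limit. The 5% level is passed about 2.2 months after placement.

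**4. The reverse direction.** A constant hazard giving 5% at 12 months is −ln(0.95)/12 = 0.00427. It implies five-year survival of 0.95⁵ = 77%. With a mean first-year rate of 5% and hazard ratio 0.75, the hazards are 0.00367 and 0.00489 and five-year failure is 20% and 25%. The 880 fillings then yield about 141 events with dropout 0.01 per month, or 181 with none, against 508 needed by the Schoenfeld formula. Power is about 40% and 48% respectively.

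**5. If the stray 20 % and 30 % were meant as five-year failure.** Hazards are −ln(0.8)/60 = 0.00372 and −ln(0.7)/60 = 0.00594, with ratio 0.63.

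| First year taken as | Lower arm | Higher arm | Mean of arms | Expected of 880 | P(more than 44) |
|---|---|---|---|---|---|
| 12 months per filling | 4.4% | 6.9% | 5.6% | 49 | about 76% |
| Calendar, 6-month placement | 3.3% | 5.2% | 4.2% | 37 | 12% |
| Calendar, 12-month placement | 2.2% | 3.5% | 2.8% | 25 | about 0.02% |

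At a mean first-year rate of exactly 5% with ratio 0.63, power with 440 per arm is about 78% (dropout 0.01 per month) to 87% (none).

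**The case against.** The strongest reply is that the sample-size paragraph is itself garbled. The stray 20 % and 30 % suggest that survival and failure were confused, so the fivefold excess may be a by-product of that slip and not a fault in the limit. This stands in part. The 20% and 30% failure reading also gives about 90% power at 440 per arm with little or no dropout, so the sample size alone does not exclude it. But it contradicts the printed hazards, the printed ratio of 0.75 and the printed 60-month proportions, and it still leaves the expected rate close to the limit.

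Several stronger conclusions are tempting and not supported:

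- A reader might infer that the rule fires on the planned course under either reading. Under the second, that needs a full 12 months of exposure per filling. On a calendar year the expected rate is below the limit, and the protocol does not say which is meant.
- A reader might infer that any failure level avoiding suspension leaves power near 40%. That holds only at a ratio of 0.75; at 0.63 power at the boundary is 78% to 87%.
- A reader might infer that the rule pools the arms, or that suspension ends the five-year follow-up. Cut off points states neither.
- A reader might infer that placement is certainly complete when the rule takes effect. The half year in Duration is only proposed, and the sample size assumes 12 months of accrual.

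A limit may also be set deliberately as a mark of unacceptable performance, whatever the planning rate. That is legitimate, and is why nothing here says that the limit must yield. It does not remove the conflict: a study planned on failure four to five times such a mark is planned on unacceptable performance.

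Finally, the definitions differ. The sample size counts fracture or crack, whereas the Criteria and Interpretation strategy sections count failure by a wider published set of criteria. The wider set would not obviously lower the rate.

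**Conclusion.** The contradiction stands as printed. The hazards that reproduce the sample size give 21.4% and 27.5% first-year failure, or 11% to 21% on a calendar year, against a limit of 5%. Suspension is then practically certain. This rests on constant monthly hazards, which the protocol states, and survives every definition of the first year tried and substantial clustering of fillings. No constant hazard meets both sections: 5% at one year goes with 77% survival at five years. Under the alternative reading of 20% and 30% five-year failure, the finding shrinks to a limit lying near the expected rate, with a probability of firing anywhere from about 0.02% to 76% because the rule's period is undefined. The documents do not settle which failure rate was intended.

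**What to change.** Reconcile Calculation of the participants and Cut off points on one assumed failure curve:

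- correct or restate whichever of the hazards, proportions, hazard ratio and power do not fit that curve, and remove or explain the stray 20 % and 30 %;
- state whether the first year is counted per filling or by calendar, and whether the rate is taken over both arms or per arm;
- name the failure definition that the rule counts;
- report the probability that the rule fires when the planning assumptions are true.

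Which section is right, and the limit itself, are for the sponsor and investigators to settle; no limit is proposed here. The cost is an amendment to a few sentences and a short calculation. If the corrected curve alters the power, the sample size needs to be looked at again; otherwise no patients or procedures are added.

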# Monitoring

A monitoring in the local dental offices will be arranged, of 10% of 880 fillings are

placed. The external examiner will check the sufficiency of study documents

(probands signed consent form, Insertion RF e.g.). Queries will get debugged.

# Study report

Each year the sponsor obtained a preliminary report of the study results in the first

second, third and forth study year. A final report will follow after the fifth year. Regular

Newsletters inform the participating dentists of the results and intermittent failures.

# Responsibilities

- LKP: [name]. [name]

OA [name]

- PI: OA [name] and calibrated examiner
  - Application for ethical board
  - Assiting statistical evaluation of data (done by [name]. math. [name])
  - Recruitment of local dental offices
  - Calibration of participating dentists
  - Contact person of participating dentists
  - SOPs (Study-Operating-Procedure)
  - Information form for participants
  - Consent form
  - Steering of baseline and Follow Ups 3,4
  - Follow Ups 1,2,5
  - Study files, documentation and archives
  - Randomization
  - Organisation of study groups per city
  - Records and communications
  - Final record
  - Publications
  - Cost control
- Examiner:
  - External Examiner (University Greifswald, University Marburg)
    - Local scheduling
    - Examiantion during Follow-up
    - Files, documentation
    - Report of adverse events to project group
    - Local data archive
    - Participation in study group
  - Dentist of local dental office
    - Files, documentation
    - Recruitment of participants
    - Local scheduling
    - Report of adverse events to project group
    - Local data archive
    - Participation in study group
- Statistics: project team ([name].-Math. [name])
  - Data Management
  - Data Safety
  - Statistical reports
  - Statistical calculations
- Medical documentalist
  - First Data entry (double entry N.N.)
  - Data management
  - Control of CRF
  - Feed back of Qeuries
- Data Safety and Monitoring Committtee ([name]. [name] and N.N.)
  - Data Management Control
  - Data Safety Control
  - Data Quality Control
  - Randomization Procedure Control
  - Veto: If quality reaches not the estimated level.
- Sponsor

o Event analysis

o Audit of files and archives

o Resources and financial support

o Organisation an arrangements of study groups and initial training

## Study File

- Permission of ethical board
- Consent forms of participants
- Insurance policy
- Documentation of treatment procedure
- Anamnestic data
- Documentation of examination parameters
  - - Local dental office:
      - Application of restoration, baseline examination
      - Date and data of examinations
      - Invitations Follow Up 1,2,3,4,5 in cooperation with project team
      - Examinations of Follow Ups 3,4 and baseline
      - Impressions regarding SOP of Follow Ups 3,4 and Baseline
    - Calibrated examiner:
      - Date and Data of examinations
      - Examinations Follow Up 1,2,5
      - Impressions regarding SOP of Follow Ups 1,2,5
      - Data file of scanning processes

## Organisation of Follow Up

- Organisation of Follow Up during study period of 5 years
- Organisation and scheduling of examinations (local dental office and
- project team)

## Communications

- Communications with project team during Follow Ups (local dental office)
- Schedule appointments in cooperation with project team
- Rejected appointments
- Communications, if adverse events occur (local dental office)
- Communication with project team
- Communications of project team
- Communications with sponsor
- Communications with local dental office

## Recruitment of participants

- Local dental office
- Control of randomization procedure by project team and DSMC

## Randomization

- Randomized controlled clinical trial
- Control of randomization by project team and DSMC

## Meeting of study groups

- project team and GC
- Organisation, invitation, training and support by GC

# Appendix

## Ethical approval

## Trail registration

This trial was approved by the ethical commision at Greifswald University (No: BB33/09) and ist registered at WHO (DRKS:-ID:DRKS00004220) at <http://drks-neu.uniklinik-freiburg.de/drks_web/setLocale_EN.do>

[figure not shown]

##
[figure not shown]

##
[figure not shown]

##
[figure not shown]

[figure not shown]

## Recruitment 1^st^ step: Numbers and areas

* incl. expansionof 25 km

## Questionnaire for the participating dentist Pseudonym: 🞏🞏🞏🞏

Location of practice: __________________________________________

**Where is your office located:**🞏 city center
🞏 city outskirts
🞏 surrounding rural areas of the city

What year was your final exam? 19 🞏🞏

For how many years is your practice? 🞏🞏

**Which practice areas do you have?**🞏 General Dentistry
🞏 Periodontology
🞏 pediatric dentistry
🞏 Orthodontics
🞏 Oral Surgery
🞏 Oral and Maxillofacial Surgery
🞏 Other _______________________

**How many dentists treat, except you, in the practice?**1 2 3 4
🞏 🞏 🞏 🞏 assistant dentist / doctors / inside
🞏 🞏 🞏 🞏 partner / inside (clinic)
🞏 🞏 🞏 🞏 partner / inside (practice sharing)
 🞏 no

**How many patients do you treat about a year?**
Health insurance (number of patients): approx ______

Private patients (invoice number): approx ______

What is the proportion of refarral patients: ____ %

Do you have a recall system?
           🞏 yes 🞏 no

How many patients engage your recall system?: ____ %

## Questionnaire for the participating patients:

Pseudonym : 🞏🞏🞏🞏

Age: 🞏🞏 Gender 🞏Female 🞏 Male

Marital Status:

🞏 married

🞏 verheiratet / separated

🞏 currently live in a committed relationship

🞏 been single, never married

🞏 divorced

🞏 widowed

How many years in schooling you have successfully completed ?

🞏 up to 8 years

🞏 8 to 10 years

🞏 more than 10 years

What is your highest degree?

🞏 still a student ( in ) without completion
🞏 Volks- or Hauptschule
🞏 Leaving school without final

🞏 High school, technical school degree, Fachschulreife

🞏 Degree of the polytechnical school

🞏 College degree, technical university, technical school
🞏 High School, general university
🞏 College degree, skilled workers with high school
🞏 other graduation

What do you think about the health of your teeth?

🞏 very good

🞏 well

🞏 satisfactory

🞏 less well

🞏 bad

How are your teeth cleaning habits?

🞏 once a week

🞏 once a day

🞏 twice a day

🞏 three times or more a day

Do you use futher oral hygiene products beside your toothbrush?

🞏 yes

🞏 no

How often were you in the last 10 years the annual bonus check ?

🞏🞏 times

When was the last time before the dentist?

🞏 this year

🞏 last year

🞏 two to three years ago

🞏 more than four years ago

## Placement Protocol (Translation from german)

**Treatment Protocol Study Center Greifswald**

**[contact]**

After the placemt of the filling, please insert the Proband’s ID, the date of birth as well as the insertion date, the treated tooth / teeth and surfaces in the clinical record file.

| Envelope | Proband’s ID | Date of birth | Insertion date | Treated tooth/teeth |
| --- | --- | --- | --- | --- |
| ***Example*** | *# 3456* | *1.2.1965* | *21.6.2009* | *15mo, 16od* |
| **1** |  |  |  |  |
| **2** |  |  |  |  |
| **3** |  |  |  |  |
| **4** |  |  |  |  |
| **5** |  |  |  |  |
| **6** |  |  |  |  |
| **7** |  |  |  |  |
| **8** |  |  |  |  |

Dental office ID

## Clinical Record File (CRF, Translation from German)

## Clinical Record File (CRF) Follow Up NU __     ____

| **Dental office ID _****______________** | |
| --- | --- |
| Date of Follow up: |  |
| Patient’s ID: | Pseudonym: |
| No:      Interponat: Replica: | |

| Treatment | 1 | 2 | 3 | 4 |
| --- | --- | --- | --- | --- |
| Tooth |  |  |  |  |
| Surface (S1, S2, S2mod) |  |  |  |  |
| A1  Surface lustre |  |  |  |  |
| B5  Fracture of material and retention |  |  |  |  |
| B6  Marginal adaptation |  |  |  |  |
| B7  Occlusal contour and wear |  |  |  |  |
| B8  Approximal anatomical form |  |  |  |  |
| B10  Patient’s view |  |  |  |  |
| C11  Postoperative (hyper-)sensitivity and tooth vitality |  |  |  |  |
| C12  Recurrence of caries (CAR), erosion, abfraction |  |  |  |  |
| C13  Tooth integrity |  |  |  |  |

See: [name] et al

# Evaluation Criteria

See: [name] et al_ FDI World Dental Federation: clinical criteria for the evaluation of direct and indirect restorations – update and clinica lexamples. Clin Oral Invest (2010) 14:349–366

#
[figure not shown]

[figure not shown]

[figure not shown]

[figure not shown]

# Notes
